### 2.8. Statistical Analysis

All statistical analyses will be performed using SAS Version 9.4 (SAS Institute Inc., Cary, NC, USA), with a two-sided significance level set at *p* < 0.05 to indicate significance. Continuous variables will be presented as medians with interquartile ranges, and categorical variables will be expressed as frequencies and percentages. The Mann–Whitney U test will be used to compare continuous variables between the two groups, and the chi-squared test will be applied for categorical variables.

For the primary outcome, event rates will be estimated using the Kaplan–Meier method, and their 95% confidence intervals will be calculated using Greenwood’s formula. The log-rank test will be used for comparisons between groups. A Cox proportional hazards model will be used to estimate the hazard ratio of the RST-guided group compared with the historical control group. Potential confounding variables will be statistically adjusted for if significant differences in baseline characteristics are observed between the two groups to minimize selection bias. For secondary outcomes, the Andersen–Gill model will be applied to recurrent event data, and a mixed-effects logistic model will be applied to events occurring within 60 days after RST decline. Other secondary endpoints will be analyzed using the same methods as the primary endpoint.

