### 2.6. Primary and Secondary Outcomes

The primary outcome is defined as a composite of heart failure hospitalization and cardiac death. Heart failure hospitalization is characterized by an admission due to worsening heart failure requiring significant up-titration of diuretic dosage, intravenous diuretic administration, or mechanical circulatory support, with a minimum of 24 h of in-hospital observation.

The secondary outcomes include feasibility, efficacy, and exploratory outcomes. The feasibility of RST telemonitoring is assessed. Efficacy outcomes encompass recurrent heart failure hospitalization, cardiac death, the occurrence of heart failure hospitalization or cardiac death within 60 days following RST decrease, heart failure hospitalization or cardiac death in patients with RST improvement (versus no improvement), heart failure hospitalization or cardiac death in patients with RST decrease (versus no decrease), and the increase of RST within one month following RST decrease. As an exploratory outcome, heart failure hospitalization or cardiac death in patients without RST decrease is also evaluated. All events will be evaluated by the independent committee.

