## 3. Expected Results

We anticipate that the ITMETHOD-HF-III study will demonstrate that mandatory, RST-guided heart failure management significantly reduces the incidence of the primary composite endpoint—heart failure hospitalization and cardiac death—compared with symptom-guided standard care in the historical control group (ITMETHOD-HF-II). Specifically, we expect that the implementation of early therapeutic interventions triggered solely by RST alerts, irrespective of clinical signs or symptoms, will enable the timely optimization of pharmacologic therapy and effectively prevent clinical decompensation.

It is projected that patients receiving RST-guided management will show a lower cumulative incidence of first heart failure hospitalization and cardiac death over the 1.5-year follow-up period. Moreover, secondary analyses are expected to reveal that the magnitude and trajectory of RST recovery following intervention will correlate with improved clinical outcomes, while persistent low RST values despite treatment may identify patients at elevated risk for adverse events. In particular, we expect that patients who achieve an RST increase to ≥30 s within 14 days after the alert threshold will exhibit favorable prognoses.

Feasibility assessments are expected to confirm the reliability and clinical usability of the automated, contactless RST monitoring system in real-world outpatient settings. We also anticipate that the study will validate the prognostic utility of RST as a non-invasive surrogate for pulmonary congestion and subclinical hemodynamic deterioration.

If the results support our hypothesis, this study will provide the first evidence that mandatory therapeutic intervention based solely on RST alerts can reduce heart failure events, thereby establishing a novel, scalable paradigm for telemonitoring-guided care in chronic heart failure management. Whether such an improvement of clinical outcomes by the RST-guided management may improve the cost-effectiveness of heart failure management remains a future concern.

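### Kaplan–Meier event rates censor non-cardiac death and so modestly overstate 1.5-year cumulative incidence; the recurrent-admission ratio needs a companion analysis that counts cardiac death

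*Protocol article*

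**What the plan says.** All references are to the protocol article.

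- Section 2.6 defines the primary outcome: "The primary outcome is defined as a composite of heart failure hospitalization and cardiac death". Death from a non-cardiac cause is not a component.
- Section 2.8 fixes the estimator: "For the primary outcome, event rates will be estimated using the Kaplan–Meier method", with 95% intervals from Greenwood's formula. It continues: "The log-rank test will be used for comparisons between groups". The effect measure follows: "A Cox proportional hazards model will be used to estimate the hazard ratio of the RST-guided group compared with the historical control group".
- The secondary list in section 2.6 begins: "Efficacy outcomes encompass recurrent heart failure hospitalization, cardiac death". For these outcomes section 2.8 says that "the Andersen–Gill model will be applied to recurrent event data" and, apart from a mixed model for events within 60 days of an RST decline, that "Other secondary endpoints will be analyzed using the same methods as the primary endpoint". Cardiac death alone therefore also receives Kaplan–Meier, log-rank and Cox.
- Section 3 describes the expected finding as a "lower cumulative incidence of first heart failure hospitalization and cardiac death over the 1.5-year follow-up period".

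The article does not mention competing or terminal events, and no sentence says how a non-cardiac death is handled.

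**The concern.** Kaplan–Meier, the log-rank test and a standard Cox model have only one place for a patient who dies of a cause outside the outcome: censoring at the date of death. For the event rate this means the patient is represented by survivors who can still be admitted. One minus Kaplan–Meier then estimates the risk in a hypothetical setting without non-cardiac death, not the share of patients who have the event within 1.5 years. Greenwood's formula is correct for the first quantity but not for the second. Cardiac death alone has the same problem.

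For recurrent admissions, any death ends observation. If frailer patients have both more admissions and earlier death, and one group has more deaths, that group loses more of its high-admission patients from the risk set, and its admission rate looks lower for that reason alone. The comparison is with historical controls, and section 4.4 concedes unmeasured confounding and changes in practice over time. Equal mortality therefore cannot be taken for granted.

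At stake are the reported 1.5-year event rates and the reading of one secondary outcome. The primary test is not at stake.

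**Working it through.** **Inputs.** Section 2.7 gives 1.5-year heart failure admission rates of 43.1% (controls) and 21.6% (anticipated under RST guidance), 52 controls and 80 planned patients. These rates are for admission rather than the full composite, and the article does not say whether 43.1% is a Kaplan–Meier estimate. I use both as stand-ins for the Kaplan–Meier figures. The non-cardiac death rate m is not in the article; I assume 2–6% per year.

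**1. Event rate.** With constant cause-specific hazards over 1.5 years:

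- One minus Kaplan–Meier = 1 − exp(−1.5 l), so l = −ln(1 − p)/1.5.
- Controls: l = −ln(0.569)/1.5 = 0.376 per year. RST-guided: l = −ln(0.784)/1.5 = 0.162 per year. By construction these return 43.1% and 21.6%.
- Cumulative incidence = l/(l + m) × [1 − exp(−1.5(l + m))].

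Controls:
- m = 0.02: 0.376/0.396 × [1 − exp(−0.594)] = 0.949 × 0.448 = 42.5%, an overstatement of 0.6 points.
- m = 0.06: 0.376/0.436 × [1 − exp(−0.654)] = 0.862 × 0.480 = 41.4%, an overstatement of 1.7 points.

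RST-guided:
- m = 0.02: 0.162/0.182 × [1 − exp(−0.273)] = 0.890 × 0.239 = 21.3%, an overstatement of 0.3 points.
- m = 0.06: 0.162/0.222 × [1 − exp(−0.333)] = 0.730 × 0.283 = 20.7%, an overstatement of 0.9 points.

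The difference of 43.1 − 21.6 = 21.5 points becomes about 21.2 (m = 0.02) or 20.7 (m = 0.06), so it is overstated by 0.3–0.8 points. The ratio stays at 0.50 when m is the same in both groups.

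In a wider range, with non-cardiac death of 2–20% over 1.5 years, the overstatement is 0.4–4.1 points in controls and 0.2–2.2 points under RST guidance. If the groups differ, the ratio moves as well: 0.475 with 5% non-cardiac death in controls and 15% under RST guidance, and 0.526 the other way round.

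**2. Against sampling error.** The 95% half-widths are 1.96 × √(0.431 × 0.569/52) = 13.5 points and 1.96 × √(0.216 × 0.784/80) = 9.0 points. For the difference the half-width is √(13.5² + 9.0²) = 16.2 points. At 2–6% per year the bias in the difference is at most 0.8/16.2, or about 5% of that.

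**3. Recurrent admissions.** This was simulated with large groups, 0.6 admissions per year, no true effect on admissions, and a gamma frailty (variance 1 or 2) multiplying both the admission and the death rate. All of these are assumptions. Andersen–Gill rate ratio for admissions alone:

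- Equal mortality: about 1.0.
- Death independent of admission risk: about 1.00, even when mortality differs.
- Death raised from 8% to 14–15% over 1.5 years: 0.96–0.97 (variance 1), 0.93 (variance 2).
- Death rate doubled from a control level of 14–15%: 0.94 (variance 1), 0.89 (variance 2).
- Death lowered from 14–15% to 8%: 1.04 (variance 1), 1.07 (variance 2).

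With death counted as an event in the same process (all simulated deaths taken as cardiac), the ratio is 1.01–1.09 when death doubles and 0.95–0.98 when it halves, so it moves in the direction of the mortality difference.

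**4. Precision of that ratio.** With variance 1, each patient has mean 0.6 × 1.5 = 0.9 admissions and variance 0.9 + 0.9² = 1.71. The standard error of the log rate ratio with 52 and 80 patients is √[(1.71/0.81)(1/52 + 1/80)] = 0.26, a 95% interval of about 0.60–1.66 around 1.

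**The case against.** The strongest reply is that the article nowhere says deaths are censored, and that competing events are often left to a full protocol or analysis plan, which is not shown. That stands as far as silence goes: the absence of a competing-risk paragraph is not a fault. But section 2.8 is not silent on the estimator. It names Kaplan–Meier and Greenwood, and these have no other way to treat a non-cardiac death.

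A second reply is that the term cumulative incidence occurs once, in the narrative on expected results, and does not define an estimand. This is fair, and I do not call it a formal contradiction. It does show which quantity the authors have in mind and how readers will take the reported rates.

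A third reply is size. The bias is a small fraction of the sampling error, the death rate is assumed, and Table 1 excludes prior stroke, hemodialysis and significant renal, liver or obstructive pulmonary disease, so high non-cardiac mortality should not be presumed. This stands and limits the weight of the point.

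Two stronger readings are tempting. A reader might infer that the primary comparison is invalid. It is not: censoring non-cardiac death is the correct construction for a cause-specific log-rank test and hazard ratio. A reader might also infer that the Andersen–Gill analysis rewards a group for losing its sickest patients. The documents do not support that as a general statement. It needs unequal mortality and a link between mortality and admission risk, neither of which they quantify. If RST guidance lowers mortality, as the authors hope, the distortion works against it. Cardiac death is also a separate efficacy outcome, so an imbalance in it would be seen.

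**Conclusion.** The point holds in a limited form. The named estimator overstates the 1.5-year probability of the composite, and of cardiac death, whenever non-cardiac deaths occur. The direction is certain and a larger sample does not remove it. The size rests on an assumed non-cardiac death rate: at 2–6% per year it is about 0.6–1.7 points at 43.1% and 0.3–0.9 points at 21.6%, small beside the sampling error. The log-rank test and Cox hazard ratio are unaffected as cause-specific analyses.

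For recurrent admissions the distortion is conditional and can favour either group. Under assumed doubling or halving of death with shared frailty, the ratio is about 0.9–1.1 when the truth is 1. That lies well within the precision this study can offer on a secondary outcome. It justifies an added analysis, not a replacement.

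**What to change.** In section 2.8, before outcome data are examined:

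- Report event rates for the composite and for cardiac death as Aalen–Johansen cumulative incidence with its own variance, with non-cardiac death as the competing event.
- Keep the log-rank test and Cox model, and label them cause-specific, with non-cardiac death censored.
- Keep the Andersen–Gill analysis of heart failure admissions as stated. Beside it, add an analysis of total heart failure hospitalizations plus cardiac death in one counting process with patient-clustered variance. It should not replace the listed outcome, because it is a different estimand, weighs a death as one admission and still censors non-cardiac death.

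The cost is a change of wording and a little more analysis work, all standard in SAS 9.4, with no new patients, visits or data on top of the cause of death that the composite already requires. The reported event rates will be slightly lower.

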### 4.3. How to Demonstrate the Clinical Implication of RST-Guided Management

Evidence from previous studies suggests that a decrease in RST below 20 s can predict heart failure hospitalization up to 28 days in advance [19]. However, the clinical efficacy of aggressive therapeutic interventions to prevent such hospitalizations in real-world daily practice remains uncertain.

In the ITMETHOD-HF-II trial, patients were encouraged to be admitted when their RST fell below 20 s. However, therapeutic decisions, including the up-titration of heart failure medications, were left to the discretion of attending physicians. In many cases, medications were not adjusted, likely because patients were asymptomatic due to early hospital admission. To unequivocally demonstrate the utility of RST in identifying subclinical heart failure and preventing hospitalizations, “mandatory” up-titration of heart failure medications is essential when RST values fall below this threshold.

Findings from the ITMETHOD-HF-II study reinforce this approach. All patients who achieved RST values of ≥30 s within 14 days by therapeutic intervention successfully avoided heart failure hospitalizations. This is a rationale why we set 30 s of RST as a therapeutic target. Based on these findings, we strongly propose repeating therapeutic adjustments until RST values exceed 30 s.

However, mandatory interventions carry potential risks, particularly in patients with hypovolemia or renal impairment, in whom hemodynamic instability may occur. Therefore, careful risk-benefit analyses are crucial to ensure the safety of mandatory interventions, especially in asymptomatic patients.

It is also important to recognize that not all participants may experience an increase in RST despite aggressive therapeutic interventions. A thorough assessment of patient characteristics, the types of interventions attempted, and clinical outcomes is necessary to identify refractory cohorts. These findings will help inform the development of tailored therapeutic strategies for these populations in future studies.

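### Comparing outcomes by RST decrease and by RST improvement with the primary endpoint's survival methods ignores that both groups form during follow-up. The bias is strong for decrease; for improvement it depends on a window the endpoint does not state.

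*Protocol article*

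**What the plan says.** Section 2.6 of the protocol article lists among the efficacy outcomes "heart failure hospitalization or cardiac death in patients with RST improvement (versus no improvement" and "heart failure hospitalization or cardiac death in patients with RST decrease (versus no decrease". Neither entry has a time window. A neighbouring outcome does have one: "the increase of RST within one month following RST decrease".

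Section 2.8 gives special models to only two secondary outcomes: Andersen–Gill for recurrent events, and mixed-effects logistic regression for events in the 60 days after an RST decline. For the rest, "Other secondary endpoints will be analyzed using the same methods as the primary endpoint". Those methods are Kaplan–Meier estimates, then "The log-rank test will be used for comparisons between groups" and "A Cox proportional hazards model will be used to estimate the hazard ratio of the RST-guided group compared with the historical control group". The article mentions no landmark, time-dependent term or reset time origin.

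A 14-day window for recovery appears only outside the endpoint definition. Section 3 expects that "patients who achieve an RST increase to ≥30 s within 14 days after the alert threshold will exhibit favorable prognoses", and section 4.3 reports from ITMETHOD-HF-II that "All patients who achieved RST values of ≥30 s within 14 days by therapeutic intervention successfully avoided heart failure hospitalizations".

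**The concern.** The primary comparison (RST-guided versus historical control) uses a group that is fixed before the clock starts. RST decrease and RST improvement are different, because they happen during follow-up. Monitoring under the protocol starts at secondary registration. Table 1 excludes patients whose RST measurement was unsuitable in both run-in weeks, and a weekly mean below 20 s is one ground for that. The second alert route in section 2.4 needs more than a month above 45 s and then a fall over 10 to 90 days. Table 2 starts RST measurement at most 21 days before secondary registration, so this route cannot be met on day 0.

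To be labelled as having a decrease, a patient must stay event-free until the decline. A patient with an early event and no earlier decline is counted under no decrease. The waiting time in the decrease group is therefore immortal time, and a fixed-group analysis counts it as time at risk.

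The two outcomes are biased in different ways:
- **Decrease:** the bias makes a decline look protective, so it can hide or reverse the prognostic signal that section 3 hopes to validate.
- **Improvement:** a patient admitted before RST recovers falls into no improvement, so the bias favours the result that section 3 expects.

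**Working it through.** The article gives no figure for either comparison, so there is none to reproduce. The check asks what the stated methods return when RST status has no relation to outcome.

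**Inputs from the article.** N = 80 and 21.6% events in the RST-guided group (section 2.7); 43.1% events, the historical control rate, as the upper case; follow-up F = 1.5 years; two-sided 5%.

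**Assumptions (not in the article).** Share of patients with a decrease by 1.5 years: 30%, 50% or 70%. Constant hazards. Event time independent of decline time.

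**Decrease, by hand (21.6% events, 50% declining).**
- Event hazard λ = −ln(1 − 0.216)/1.5 = 0.1622 per year. Decline hazard δ = −ln(0.5)/1.5 = 0.4621. Sum a = 0.6243, and e^(−aF) = 0.784 × 0.5 = 0.392.
- Events with no earlier decline: λ(1 − 0.392)/a = 0.1580 per patient, or 12.6 in 80. Events after a decline: 0.216 − 0.1580 = 0.0580, or 4.6 in 80.
- Person-years labelled no decrease: (λ/a²)[1 − 0.392(1 + aF)] + 1.5 × 0.392 = 0.100 + 0.588 = 0.688, or 55.1 in 80.
- All person-years: 0.216/0.1622 = 1.331, or 106.5 in 80. This leaves 51.5 for the decrease group.
- True time before a decline: 0.608/0.6243 = 0.974, or 77.9 in 80. True time after a decline: 106.5 − 77.9 = 28.6. So 51.5 − 28.6 = 22.9 person-years of the decrease group are immortal.
- Fixed-group rates: 4.64/51.5 = 0.090 and 12.64/55.1 = 0.229. The ratio is **0.39** where the truth is 1.
- With time split at the decline: 4.64/28.6 = 0.162 and 12.64/77.9 = 0.162. The ratio is **1.0**.

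**Decrease, by simulation** (2,000–4,000 replicates; label reached before event or censoring; clock from registration):

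| Events | Declining | Median HR (truth 1) | False rejection |
|---|---|---|---|
| 21.6% | 30% | 0.42 | 18% |
| 21.6% | 50% | 0.39 | 43% |
| 21.6% | 70% | 0.32 | 66% |
| 43.1% | 30–70% | 0.33–0.43 | 39–91% |

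A separate run over the same assumptions gave HR 0.32–0.44 and 17–89% rejection. With decrease as a time-dependent covariate, HR is 0.96–1.01 and rejection 3.9–5.5%.

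If a decline truly doubles the hazard, the fixed-group HR is 0.59–0.83. If it triples the hazard (21.6% events, 50% declining), the HR is 1.10.

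**Improvement, no true association.** The result depends on the definition:

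| Definition | HR (truth 1) | False rejection |
|---|---|---|
| No window, improvers versus all other patients, median 30 days to improve | 0.29–0.41 | 19–92% |
| No window, among decliners, registration clock, 50–70% declining, median 30–90 days to improve | 0.33–0.52 | about 28–41% in the runs with 70% declining |
| As above, alert clock | 0.04–0.17 | about 62–84% in the runs with 70% declining |
| 14-day window, improvers versus all other patients | 0.44–0.48 | 3–38% |
| 14- or 30-day window, alerted patients only, even risk | 0.86–1.04 | 3–6% |
| 14-day window, alerted patients, risk clustered after the alert | 0.74–0.99 | 3–8% |
| 30-day window, alerted patients, risk clustered after the alert | 0.52–0.81 | 9–30% with 14-day median recovery |

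The clustered rows assume 40 alerted patients and a 60-day event risk of 10–30%. In the 14-day row, HR is about 0.95–0.98 over one year and 0.74–0.84 over 60 days. A landmark at the end of the window gives HR 0.96–1.06 and rejection 3–6% (even-risk scenarios).

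**The case against.** The article names methods, not coding. A Cox model can take a time-dependent covariate, and Kaplan–Meier and log-rank can run from a landmark. An unseen SAP may settle the time origin and labelling. Labelling by RST over the whole 1.5 years, whether or not an event came first, gives HR 0.99–1.02 under the null.

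Part of this stands: the article does not spell out the labelling, and the figures above hold for the labelling described. But the sentence does choose a method. The primary methods compare groups known at time zero, and section 2.8 gives other models to outcomes judged to need them. Whole-period labelling is no remedy, because the label can then come after the event.

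Three stronger readings are tempting and not supported.
- **That immortal time alone creates a strong false association for both outcomes.** For improvement within 14 days among alerted patients, the bias is small. The 14-day expectation in section 3 would not be confirmed automatically.
- **That the ITMETHOD-HF-II observation in section 4.3 is an artefact.** A patient admitted before recovery cannot count as a responder, so the observation is exposed to the same problem. But the window there is 14 days, where the bias is small, and the article does not say how that trial was analysed.
- **That the trial's main conclusion is at risk.** It rests on the primary composite against historical controls, which these groupings do not touch.

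**Conclusion.** The concern holds firmly for RST decrease. With a label set by a decline before the event and a clock from registration, a null effect appears as HR of about 0.3–0.45 with 17–89% false rejection. A truly harmful decline can look neutral or protective. The size rests on the assumed 30–70% of patients declining and on constant hazards. At 21.6% events there are only about 17 events (80 × 0.216), so the false HR is strong but often not significant.

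For RST improvement the direction is clear, but the size is open because section 2.6 gives no window. It is large with none, moderate with 30 days and fast recovery, and small with 14 days among alerted patients. Severity is moderate: two secondary efficacy outcomes are affected and the primary comparison is not.

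**What to change.** Replace the reference to the primary methods for these two outcomes.

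- **Decrease:** enter RST decrease as a time-dependent covariate in the Cox model, with each patient counted as not decreased until the decline occurs.
- **Improvement:** define it by RST status in a fixed window after the alert, for example the 14 days that the article already names, and compare only patients who had an alert. Start the analysis from a landmark at the end of that window among those still event-free, or use a time-dependent covariate.
- **Curves:** draw Kaplan–Meier curves only from the landmark, not from registration or from the alert.

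The cost is a change of wording and some extra programming. The landmark drops patients whose event came before it; report how many. No data collection or patient management changes.
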